## Abstract

**Background:**

Observational data shows that postterm pregnancy (≥42 gestational weeks, GW) and late term pregnancy (≥41 GW), as compared to term pregnancy, is associated with an increased risk for adverse outcome for the mother and infant. Standard care in many countries is induction of labour at 42 GW. There is insufficient scientific support that induction of labour at 41 GW, as compared with expectant management and induction at 42 GW will reduce perinatal mortality and morbidity without an increase in operative deliveries, negative delivery experiences or higher costs. Large randomised studies are needed since important outcomes; such as perinatal mortality and hypoxic ischaemic encephalopathy are rare events.

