### Secondary outcome measures- neonates

Admittance to neonatal intensive care unit, birth weight, macrosomia (>4.5 kg), Apgar score <4 at 5 min, therapeutic hypothermia, neonatal jaundice, pneumonia, sepsis, costs.

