### Secondary outcome measures-mothers

Use of epidural analgesia, caesarean section, assisted vaginal delivery, duration of labour, episiotomy, perineal lacerations III-IV, shoulder dystocia, postpartum hemorrhage (>1000 ml), chorioamnionitis, wound infection, urinary tract infection, endometritis, sepsis, costs.

Data on women’s attitudes, experiences and health-related quality of life will be collected, only in the Region Vastra Götaland subpopulation, by questionnaires (web based or postal).

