The primary statistical analysis will be the comparison of primary composite outcome (stillbirth, neonatal mortality and morbidity) between the two randomised groups with two-sided Fisher’s exact test on the intention to treat (ITT) [46] populations at significance level 0.05. Adjustments for baseline variables if necessary and interaction analyses will be performed with multivariable logistic regression analyses. For variables with interactions *p* <0.10 with primary efficacy variable, subgroup analyses will be performed. Women with spontaneous labour or prelabour rupture of the membranes (PROM) after randomisation but before planned induction will be included in the statistical analysis according to ITT. Women with pregnancy complications after randomisation indicating any need of intervention are included in the statistical analysis according to ITT. Foetuses/newborns with lethal birth defects will be excluded in the analysis of stillbirth, neonatal mortality and morbidity. The median, 95 % CI, quartiles, means and SD are calculated when appropriate. The Mann–Whitney U test is used to compare differences between the two groups concerning continuous variables, Fisher’s exact test for dichotomous variables, Mantel-Haenszel Chi-square test for ordered categorical variables and Chi-square test for unordered categorical variables.

The statistician will be blinded to group and intervention. Otherwise blinding is not possible for practical reasons.

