### Cost-effectiveness analyses

Cost-effectiveness analyses will be performed comparing induction at GW 41^+0^ with induction at GW 42^+0^. The primary measures of effectiveness will be a composite of stillbirth, neonatal mortality and neonatal morbidity (i.e. primary outcome) [47]. A broad range of sensitivity analyses will be performed, which includes calculating CIs of the cost-effectiveness measures, using bootstrapping [47]. In order to extrapolate the outcomes observed in this study to a longer time span we will utilize a simulation model. The model will be constructed and parameterized using estimates of relevant parameters obtained within the project. Moreover, associations between neonatal outcomes and health outcomes later in life that was not studied in this project will be collected from the epidemiology literature. Initially, two modelling structures will be considered: a Markov structure and a discrete event structure [48]. The typical Markov model uses a cohort and state-transition technique, while the discrete event structure means that simulations are event-based and performed at the individual level. The choice between these two main alternatives will be performed according to the guidelines provided in Brennan et al. [48].

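### Costs are secondary outcomes but are not exempted from the Mann–Whitney rule for continuous variables, and a rank test does not address the difference in mean cost

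*Protocol article*

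**What the plan says.** Costs close both lists of secondary outcomes. The neonatal list ends "therapeutic hypothermia, neonatal jaundice, pneumonia, sepsis, costs" and the maternal list ends "chorioamnionitis, wound infection, urinary tract infection, endometritis, sepsis, costs".

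The Statistical analysis section then assigns tests by type of variable. For continuous variables it says "The Mann–Whitney U test is used to compare differences between the two groups concerning continuous variables". No variable is exempted. On description, the same section says "The median, 95 % CI, quartiles, means and SD are calculated when appropriate".

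The Cost-effectiveness analyses section compares the two policies, with the primary composite as the measure of effectiveness. Its sensitivity analyses include "calculating CIs of the cost-effectiveness measures, using bootstrapping". It names no estimate or test for the between-group difference in cost alone, and it does not say that costs are taken out of the general rule.

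The Abstract's Background names cost among the open questions: whether induction at 41 weeks lowers mortality and morbidity "without an increase in operative deliveries, negative delivery experiences or higher costs".

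**The concern.** Whether a policy leads to higher costs is a question about total cost, and so about mean cost per woman and infant. The incremental cost in a cost-effectiveness analysis is a difference in means as well. The Mann–Whitney test has a different null: that a random woman in one arm is as likely to cost more as to cost less than a random woman in the other.

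The two questions can separate here. The Discussion expects more inductions in the early arm, and the induction section keeps induced women in hospital until delivery. That may add a small cost for many women. The sample-size paragraph expects the primary outcome to fall from 2.74 % to 1.84 %, which may save a large cost for few. Ranks register the first effect and nearly ignore the second. At stake is a report in which the p-value for the secondary outcome costs points one way and the incremental mean cost points the other.

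**Working it through.** The article gives no cost figure for this trial, so there is no stated figure to reproduce. The sample size of 10 038 concerns the primary outcome and has no bearing on this point.

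**Inputs from the article.** 5 019 women per arm less 10 % dropout: 5 019 × 0.9 = 4 517 analysed per arm. Primary outcome 2.74 % (late) and 1.84 % (early), used as the share of costly cases; the difference is 0.009.

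**Assumptions.** Routine cost is lognormal with mean 1 (base unit) and CV 0.4. Routine cost in the early arm is higher by a fraction s. Each primary-outcome case adds a cost K.

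**Difference in means (early − late).** s − 0.009 K. It is zero when K = s / 0.009, that is, K = 1.1, 2.2, 3.3 and 5.6 base units for s = 1, 2, 3 and 5 %.

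**What the rank test sees.** Let θ be the probability that a random early-arm woman costs more than a random late-arm woman (ties counted half); the null is θ = 0.5.
- Standard error under the null: about √(1/(6n)) = √(1/27 102) = 0.0061.
- Rare cases: even if every case outranks all other women, 0.9 points fewer of them lowers θ by at most about 0.009 × 0.5 = 0.0045, or 0.74 standard errors, however large K is.
- Routine shift: θ − 0.5 = Φ(ln(1+s)/(σ√2)) − 0.5, with σ = √ln(1 + 0.4²) = 0.385. This gives 0.0073, 0.0145, 0.0216 and 0.0357 for s = 1, 2, 3 and 5 %, or 1.20, 2.39, 3.56 and 5.87 standard errors.
- Net of 0.74: 0.46, 1.65, 2.82 and 5.13. The chance of exceeding 1.96 is then about 7 %, 38 %, 80 % and over 99 %.

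**Simulation of the same model (400 trials per row).** Share of trials declaring early induction significantly dearer:

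| s | Mann–Whitney, means equal | Welch, means equal | Mann–Whitney, K 1.5 times larger | Welch, K 1.5 times larger |
|---|---|---|---|---|
| 1 % | 5.5 % | 1.5 % | 5.5 % | 0.5 % |
| 2 % | 36 % | 2.8 % | 35 % | 0.5 % |
| 3 % | 77 % | 1.5 % | 79 % | 0.5 % |
| 5 % | 100 % | 3.5 % | 99.8 % | 0.3 % |

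With K 1.5 times larger, the true mean difference is s − 1.5 s = −0.5 s, so early induction is cheaper on average. The rank test hardly notices.

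**Sensitivity to the direction of the routine shift (300 trials per setting).** Assumptions: CV 0.6; induction in 85 % (early) and 35 % (late) of women, adding 10 % of base; costly cases 1.84 % and 2.74 % with exponential cost of mean 5 or 10 base units; and an extra routine cost in the late arm. The net routine shift is 0.10 × (0.85 − 0.35) − late-arm cost = 0.05 − late-arm cost. The rare cases add −0.009 × 5 = −0.045 or −0.009 × 10 = −0.09 to the mean difference.

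| Late-arm routine cost | Net routine shift | Mean difference (5; 10 units) | Mann–Whitney result |
|---|---|---|---|
| 0 | +0.05 | +0.005; −0.04 | early dearer in 98–99 % |
| 2.5 % of base | +0.025 | −0.02; −0.065 | early dearer in 40–44 % |
| 5 % of base | 0 | −0.045; −0.09 | early dearer in 0.7 % |
| 7.5 % of base | −0.025 | −0.07; −0.115 | early cheaper in 86–89 % |

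In the last row the rank test and the means agree in sign. In the second row they conflict in a large share of trials.

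**The case against.** The strongest reply is that nowhere does the article say costs will be tested by Mann–Whitney. The rule is a generic default by variable type, means and SD are among the planned summaries, and the economic question has its own section. The Abstract even names the secondary outcome as cost effectiveness. On a natural reading, the costs at the end of the two lists are inputs to that section, and the specific section prevails over the default. The article is also a condensed account, and a fuller plan may already settle the matter.

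Much of this stands. The application to costs is an inference from a general rule, and the main economic conclusion would probably rest on the cost-effectiveness analysis. But costs are named as outcomes in their own right, the rule has no exception, and the cost-effectiveness section does not claim to replace it. What the article fixes, read literally, is a test of the wrong quantity for a named outcome. That differs from leaving a detail to another document.

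A reader might go further and infer that the rank test will almost surely report early induction as dearer. The article does not support that. It gives no unit costs. Women in the late arm have follow-up during week 41, and the Background reports lower cost with induction in the Canadian multicentre trial, with a caveat about its age. The sign of the routine-cost shift is therefore unknown, and the second table shows that a modest late-arm cost removes or reverses the effect.

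**Conclusion.** The point holds in a limited form. As written, the general rule covers the secondary outcome costs and gives a rank test where the question is about means, so its p-value could disagree with the trial's own incremental mean cost. How often, and in which direction, depends on assumed costs. Disagreement is negligible at a net routine-cost shift of about 1 %, or where late-arm costs offset the shift. It is near certain at a net shift of about 5 % in the early arm. These figures also take maternal and neonatal costs together, although the article lists them separately.

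The primary outcome, the sample size and the cost-effectiveness analysis are unaffected. The article does not support the claim that the trial will report contradictory cost results, only that its wording allows them. This is a cheap improvement.

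**What to change.** In the Statistical analysis section, exempt costs from the Mann–Whitney rule with one sentence, for example:

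> Costs will be compared by randomised group (ITT) as the difference in arithmetic mean cost, for mothers, neonates and the mother–infant pair, with a bootstrap 95 % CI from the same replicates as the cost-effectiveness analysis; medians are descriptive only.

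The secondary cost outcome for the pair and the incremental cost in the cost-effectiveness analysis are then the same estimate and cannot disagree. If a fuller plan already says this, only the article's wording needs aligning.

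The change needs no new data and reuses a planned method. The small downside is a wider interval for mean cost, because it reflects the rare, expensive cases.

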### Cost-effectiveness analyses

Cost-effectiveness analyses will be performed comparing induction at GW 41^+0^ with induction at GW 42^+0^. The primary measures of effectiveness will be a composite of stillbirth, neonatal mortality and neonatal morbidity (i.e. primary outcome) [47]. A broad range of sensitivity analyses will be performed, which includes calculating CIs of the cost-effectiveness measures, using bootstrapping [47]. In order to extrapolate the outcomes observed in this study to a longer time span we will utilize a simulation model. The model will be constructed and parameterized using estimates of relevant parameters obtained within the project. Moreover, associations between neonatal outcomes and health outcomes later in life that was not studied in this project will be collected from the epidemiology literature. Initially, two modelling structures will be considered: a Markov structure and a discrete event structure [48]. The typical Markov model uses a cohort and state-transition technique, while the discrete event structure means that simulations are event-based and performed at the individual level. The choice between these two main alternatives will be performed according to the guidelines provided in Brennan et al. [48].

### Serious adverse events

The following serious adverse events (SAE) will be identified: stillbirth, neonatal death, severe neonatal morbidity, defined as intraventricular haemorrhage, asphyxia or MAS with admission to NICU, maternal death, severe maternal morbidity defined as admission to intensive care unit and events related to induction of labour e.g. uterine rupture. All SAEs are reported to the main investigators, who will report to the Data and Safety Monitoring Board (DSMB).

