**Methods/Design:**

A total of 10 038 healthy women ≥18 years old with a normal live singleton pregnancy in cephalic presentation at 41 GW estimated with a first or second trimester ultrasound, who is able to understand oral and written information will be randomised to labour induction at 41 GW (early induction) or expectant management and induction at 42 GW (late induction). Women will be recruited at university clinics and county hospitals in Sweden comprising more than 65 000 deliveries per year. Primary outcome will be a composite of stillbirth, neonatal mortality and severe neonatal morbidity. Secondary outcomes will be other adverse neonatal and maternal outcomes, mode of delivery, women’s experience, cost effectiveness and infant morbidity up to 3 months of age. Data on background variables, obstetric and neonatal outcomes will be obtained from the Swedish Pregnancy Register and the Swedish Neonatal Quality Register. Data on women’s experiences will be collected by questionnaires after randomisation and 3 months after delivery. Primary analysis will be intention to treat. The statistician will be blinded to group and intervention.

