## Outcome measures

### Primary outcome measure

A composite of stillbirth, neonatal mortality and neonatal morbidity. Stillbirth is defined as intrauterine foetal death of a foetus that was alive at randomisation. Neonatal mortality is defined as live births with death day 0–27. Neonatal morbidity is defined as at least one of the following variables: Apgar score <7 at 5 min, metabolic acidosis defined as pH <7.05 and base deficit >12 mmol/l in umbilical artery or pH <7.00 in umbilical artery, HIE I-III, intracranial haemorrhage, neonatal convulsions, meconium aspiration syndrome (MAS), mechanical ventilation, obstetric brachial plexus injury.

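### One SAE class is tied to induction of labour, so uterine rupture and similar events would be recorded unevenly between the arms; the neonatal SAE wording also needs reconciling with the primary outcome

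*Protocol article*

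**What the plan says.** The Serious adverse events section of the protocol article lists six classes: stillbirth, neonatal death, severe neonatal morbidity, maternal death, severe maternal morbidity (admission to intensive care), and "events related to induction of labour e.g. uterine rupture". Reports go to the main investigators, who pass them to the DSMB.

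Other sections bear on the last class:

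- Discussion: a higher proportion of inductions is expected in the early group.
- Labour induction: women in the control group who reach 42 completed weeks are also induced.
- Statistical analysis: only the statistician is blinded.
- Secondary outcome measures-mothers: uterine rupture does not appear.

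For the newborn, the SAE class is "severe neonatal morbidity, defined as intraventricular haemorrhage, asphyxia or MAS with admission to NICU". The Primary outcome measure section has a longer morbidity list with no NICU condition. It opens "Neonatal morbidity is defined as at least one of the following variables: Apgar score <7 at 5 min, metabolic acidosis", gives the cord-gas limits, and continues with "HIE I-III, intracranial haemorrhage, neonatal convulsions, meconium aspiration syndrome (MAS), mechanical ventilation, obstetric brachial plexus injury". That section speaks of neonatal morbidity without the word severe. The abstract calls the same endpoint a "composite of stillbirth, neonatal mortality and severe neonatal morbidity".

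**The concern.** Whether an event belongs to the last class depends on how labour began, and the allocated policies are designed to make that differ between arms. A harm that can follow either induced or spontaneous labour would then enter the SAE record more readily in the early arm. Because staff know the allocation, the judgement that an event is related to induction is also made unblinded. Uterine rupture is not a listed secondary outcome, so the article names no second place where it would be counted the same way in both arms. A reader of SAE counts by arm could take a reporting difference for a difference in harm.

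The neonatal SAE class raises a smaller issue. It uses a term that the abstract applies to the primary outcome, gives it different content, and relies on the word asphyxia, which the article does not define. Centres could apply it differently.

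**Working it through.** **Induction-tied class.** No induction rate by arm is given, so the size can only be illustrated. Let p_E and p_L be the proportions induced in the early and late arms. Let r be a rupture risk that is equal in both arms and unrelated to labour onset. Let s be the share of ruptures after spontaneous labour that reach the SAE record through another class (stillbirth, neonatal death, listed neonatal morbidity, maternal death or intensive care).

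Reported risk in an arm = r × [p + (1 − p) × s]

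Reporting ratio, early to late = [p_E + (1 − p_E)s] / [p_L + (1 − p_L)s]

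The ratio exceeds 1 whenever p_E > p_L and s < 1. The Discussion supplies the first condition.

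Assume p_E = 0.90 and p_L between 0.30 and 0.50:

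| s (assumed) | p_L = 0.50 | p_L = 0.30 |
|---|---|---|
| 0 | 0.90/0.50 = 1.8 | 0.90/0.30 = 3.0 |
| 0.5 | 0.95/0.75 = 1.27 | 0.95/0.65 = 1.46 |
| 1 | 1.0 | 1.0 |

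The range 1.8 to 3 is thus the upper end under these induction rates. It shrinks as more ruptures are caught elsewhere. No absolute number of events can be derived, because the article gives no rupture rate.

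**Neonatal wording, term by term.**

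| Primary outcome morbidity | Neonatal SAE class |
|---|---|
| Apgar <7 at 5 min; metabolic acidosis; HIE I-III | Only through asphyxia, undefined |
| Intracranial haemorrhage | Intraventricular only |
| MAS | MAS with NICU admission |
| Convulsions; mechanical ventilation; brachial plexus injury | Not named |

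It is also unclear whether the NICU condition applies to MAS alone or to all three SAE items.

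**How far asphyxia matters.** The Statistical analysis section budgets the control-arm rate from components: HIE 0.22 + MAS 0.36 + brachial plexus injury 0.05 + Apgar <7 1.58 + deaths 0.53 = 2.74 %, which reproduces the stated figure. Taking these as additive, as the article does, and assuming that every MAS and asphyxia case is admitted to NICU, the share of 2.74 % that the SAE list could capture is at most:

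- asphyxia covers neither HIE nor low Apgar: (0.53 + 0.36)/2.74 = 32.5 %
- asphyxia covers HIE only: (0.53 + 0.36 + 0.22)/2.74 = 40.5 %
- asphyxia covers HIE and every Apgar <7: (2.74 − 0.05)/2.74 = 98.2 %

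The share not captured therefore runs from about 2 % to 68 %, depending on one undefined word. The NICU condition could raise it by an amount that the article does not give. Acidosis, intracranial haemorrhage, convulsions and ventilation have no stated rate and cannot be placed in this sum.

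**The case against.** An induction-related class exists to detect harm from the intervention. It also applies in the control arm, where women still undelivered are induced. Women with previous caesarean section or other uterine surgery are excluded, which removes one group from the population. A rupture with serious consequences would usually meet another class. A site might also read the class as naming types of event and report every rupture. These points limit the size of the problem, but they do not remove it. A rupture after spontaneous labour without another listed consequence is still not clearly reportable, and different readings by different centres would make the counts less comparable.

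Several stronger readings are tempting but not supported:

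- **Safety monitoring as a whole is lopsided, or harms of waiting go uncounted.** Stillbirth, neonatal death, asphyxia, MAS, maternal death and intensive care admission are SAEs in both arms whatever the onset of labour.
- **A rupture after spontaneous labour counts only through maternal death or intensive care.** It also counts if it results in stillbirth, neonatal death or listed neonatal morbidity.
- **The DSMB sees only SAEs.** The Data safety section gives it periodical reviews and does not limit their content. The Discussion says that outcomes are collected continuously through registers.
- **Most of the primary endpoint is missing from the SAE list.** This depends on what asphyxia covers, and both death components are SAEs. An SAE list need not equal an efficacy endpoint, and leaving out isolated low Apgar scores can be a reasonable choice.

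On terminology, the operative outcome definition does not use the word severe. The clash of labels lies between the abstract and the SAE section only.

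**Conclusion.** The point holds for one SAE class. As written, it ties reporting of events such as uterine rupture to induction, which the article expects to be more frequent in the early arm, and relatedness is judged with the allocation known. The direction of the imbalance follows from the article. The size does not: the ratio of 1.8 to 3 rests on assumed induction rates, an onset-independent risk and no capture through other classes. If induction itself affects rupture risk, the class as worded cannot separate that effect from the reporting difference, whereas a count of all ruptures in each randomised arm would compare the two policies.

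The neonatal wording is a secondary matter of clarity. The definitions differ and one term is undefined, but it is not shown that monitoring would miss most primary events. Neither issue affects the sample size or the primary analysis.

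**What to change.** Replace the induction-related class with named maternal events, for example uterine rupture, recorded in both arms regardless of how labour began. Suspected relation to induction can be kept as a separate field on the report, so that the intended signal is not lost.

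For the neonatal class:

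- reconcile intraventricular with intracranial haemorrhage;
- tie asphyxia to the Apgar, cord-gas and HIE criteria already in the Primary outcome measure section;
- state which items the NICU condition qualifies;
- add convulsions and mechanical ventilation, or state that they are deliberately left out;
- use a label distinct from the abstract's term for the primary outcome.

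The cost is a wording change and slightly more SAE reports for sites to forward.
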